## Abstract

**Background:**

Despite pharmacological treatments, patients undergoing cardiac surgery experience severe anxiety and pain, which adversely affect outcomes. Previous work examining pediatric and nonsurgical adult patients has documented the effectiveness of inexpensive, nonpharmacological techniques to reduce anxiety and pain as well as health care costs and length of hospitalization. However, the impact of nonpharmacological interventions administered by a dedicated *comfort coach* has not been evaluated in an adult surgical setting.

**Objective:**

This trial aims to assess whether nonpharmacological interventions administered by a trained *comfort coach* affect patient experience, opioid use, and health care utilization compared with usual care in adult cardiac surgery patients. This study has 3 specific aims: assess the effect of a *comfort coach* on patient experience, measure differences in inpatient and outpatient opioid use and postoperative health care utilization, and qualitatively evaluate the *comfort coach* intervention.

**Methods:**

To address these aims, we will perform a prospective, randomized controlled trial of 154 adult cardiac surgery patients at Michigan Medicine. Opioid-naive patients undergoing first-time, elective cardiac surgery via sternotomy will be randomized to undergo targeted interventions from a *comfort coach* (intervention) versus usual care (control). The individualized *comfort coach* interventions will be administered at 6 points: preoperative outpatient clinic, preoperative care unit on the day of surgery, extubation, chest tube removal, hospital discharge, and 30-day clinic follow-up. To address aim 1, we will examine the effect of a *comfort coach* on perioperative anxiety, self-reported pain, functional status, and patient satisfaction through validated surveys administered at preoperative outpatient clinic, discharge, 30-day follow-up, and 90-day follow-up. For aim 2, we will record inpatient opioid use and collect postdischarge opioid use and pain-related outcomes through an 11-item questionnaire administered at the 30-day follow-up. Hospital length of stay, readmission, number of days in an extended care facility, emergency room, urgent care, and an unplanned doctor’s office visit will be recorded as the primary composite endpoint defined as total days spent at home within the first 30 days after surgery. For aim 3, we will perform semistructured interviews with patients in the intervention arm to understand the *comfort coach* intervention through a thematic analysis.

**Results:**

This trial, funded by Blue Cross Blue Shield of Michigan Foundation in 2019, is presently enrolling patients with anticipated manuscript submissions from our primary aims targeted for the end of 2020.

**Conclusions:**

Data generated from this mixed methods study will highlight effective nonpharmacological techniques and support a multidisciplinary approach to perioperative care during the adult cardiac surgery patient experience. This study’s findings may serve as the foundation for a subsequent multicenter trial and broader dissemination of these techniques to other types of surgery.

**Trial Registration:**

ClinicalTrials.gov NCT04051021; https://clinicaltrials.gov/ct2/show/NCT04051021

**International Registered Report Identifier (IRRID):**

DERR1-10.2196/21350

## Introduction

### Nonpharmacological Interventions

Adults undergoing inpatient surgery commonly develop both severe perioperative anxiety [1-5] (28%-70% of patients) and postoperative pain (54%-74% with moderate-to-severe pain at discharge), [6,7] both of which may significantly affect patient outcomes [8-11]. Nonpharmacological interventions such as distraction techniques, guided imagery, music, and art have been found to be inexpensive complements to pharmacologic treatments, effectively reducing both anxiety and acute and chronic pain [12-14] in pediatric [15] and hospitalized nonsurgical adult patients [16-19] when administered routinely by a dedicated child life specialist *comfort coach*. However, the impact of nonpharmacological interventions and the role of a comfort coach in an adult surgical setting has not been evaluated.

### Certified Child Life Specialists

Certified child life specialists are frontline health care professionals trained to provide psychosocial care to pediatric patients and families facing stressful medical experiences. Child life specialists conduct thorough assessments and build therapeutic relationships with patients and families to support them to cope and protect emotional safety. Individualized interventions include fostering healing environments, therapeutic play, nonpharmacological pain management, procedural preparation, diagnosis teaching, sibling support, medical play, and bereavement support. Child life specialists obtain a bachelor’s degree with an emphasis on psychology, education, and human development. They complete comprehensive clinical training, pass a certification exam, and maintain certification through targeted continuing education [20].

### Applications in the Pediatric Setting and Translation to the Adult Setting

Child life specialists work with pediatric patients to teach individualized coping strategies to mitigate anxiety and manage both acute and chronic pain. Play is the universal language of all children, and play-based coping strategies foster expression and promote a sense of control and mastery. Nonpharmacological interventions effective in pediatric and adolescent patients include calm breathing techniques, distraction, guided imagery, art, muscle relaxation, music, environmental modification, and comfort positioning [20]. The child life specialist’s role has resulted in reduced pain, anxiety, use of analgesics, and length of stay [16]. We often assume that adults can handle medical stressors and employ coping skills, but many adults do not have such skills established [21]. In addition, this has resulted in underestimating adult patients’ pain effects [22] and often not addressing pain with known effective nonpharmacological interventions in combination with pain medication [13]. Building on the effectiveness and essential skills that have been dedicated to pediatric patients can facilitate opportunities for adult patients to reframe health care experiences and provide coaching through pain and anxiety, adding to their coping skills to support comfort. Applying child life strategies across the age span can further enhance the human experience of health care [23].

### Conceptual Model

We propose that providing a dedicated, trained comfort coach administering nonpharmacological interventions will improve cardiac surgery outcomes, including anxiety, self-reported pain, opioid use, and health care utilization. Periprocedural nonpharmacological approaches are well established in pediatrics [24,25], especially for needle-related pain [26]. Nonpharmacological approaches to acute pain management are rooted in the *gate-control theory* [27,28]. This theory suggests that descending nerve impulses from the brain, including thoughts, beliefs, emotions, and attention, can influence the ascending pain signal from tissue damage. In the context of surgery, anxiety may heighten pain, whereas attention focused on pleasant activity might decrease pain. In this context, many nonpharmacological interventions mitigate anxiety, which mediates pain perception, with both decreased anxiety and perception of pain affecting patient outcomes (Figure 1).

**Figure 1 figure1:**
[figure not shown]
Conceptual model. This conceptual model demonstrates the hypothesized effect of nonpharmacological interventions on the outcomes in this study rooted in gate-control theory.

### Rationale for the Study

Approximately 300,000 adults undergo cardiac surgery in the United States each year [29], with 90-day episode payments combined to exceed US $15 billion [30-32]. Cardiac surgery through a sternotomy has been shown to cause severe anxiety and pain that persist in spite of pharmacologic pain control with opioids [5,33,34], with up to 81% reporting some pain at 1 month [35] and up to 43% reporting persistent pain at 1 year [36]. Rates of persistent opioid use and long-term opioid dependence in cardiac surgery patients have increased 8-fold over the past 15 years, resulting in higher postoperative complication rates, prolonged hospital length of stay, and increased health care costs [37]. Moreover, opioid prescription sizes remain high, and overprescribing is common [38-47]. Whereas assessments of individual nonpharmacological interventions such as preoperative education [48,49], massage [50], and music [34] have demonstrated an improvement in self-reported pain scores after cardiac surgery, differences in opioid use have not been reported. Furthermore, individualized nonpharmacological interventions by a comfort coach have been shown to reduce the length of hospital stay [15,51] and health care costs [52,53] in pediatric patients, prompting the establishment of child life services as a *quality benchmark* and *indicator of excellence in pediatric care*, [15,54]. In contrast, these techniques have not been studied in adult cardiac surgery patients.

Data generated by this study may highlight effective techniques and support a multidisciplinary approach to nonpharmacological interventions to decrease pain, opioid use, anxiety, and health care utilization while increasing patient comfort and overall satisfaction during the adult cardiac surgery patient experience.

## Methods

### Overall Study Design

We will perform a prospective, double-armed, randomized, controlled trial of 154 cardiac surgical patients at a large academic center to assess whether nonpharmacological interventions by a trained comfort coach affect patient experience, opioid use, and health care utilization as compared with usual care. The individualized comfort coach interventions will be administered at 6 time-points: (1) at the preoperative clinic, (2) on the day of surgery, (3) at extubation, (4) at chest tube removal, (5) at hospital discharge, and (6) at the 30-day clinic follow-up.

This study has 3 specific aims: (1) assess the effect of a comfort coach on patient experience, (2) measure differences in inpatient and outpatient opioid use and postsurgical health care utilization, and (3) qualitatively evaluate the effectiveness of the comfort coach intervention. Toward aim 1, we will use validated survey metrics to capture anxiety and depression (preoperative clinic, discharge, 30-day follow-up, and 90-day follow-up), functional status (preoperative clinic and 30-day follow-up), surgery-related psychological stress (30-day follow-up), patient-reported in-hospital pain (discharge), and patient experience (30-day follow-up). Toward aim 2, we will compare inpatient and postdischarge opioid use and patient-reported outcomes, including pain scores and pain management practices between groups. In addition, the composite primary endpoint of the study will be recorded as the total number of days spent at home out of the first 30 after surgery, incorporating hospital length of stay, readmissions, number of days in an extended care facility, emergency room, urgent care, and unplanned doctor visits. Aim 3 will include semistructured interviews of patients in the intervention group to understand the role, impact, and acceptability of a comfort coach.

All requirements for conducting human subjects research at the University of Michigan have been met. The study protocol has been reviewed, and the University of Michigan Institutional Review Board has approved this trial (quantitative, HUM00161399, and qualitative, HUM00170502). This clinical trial has been registered at ClinicalTrials.gov (NCT04051021).

### Patient Enrollment and Randomization

Cardiac surgical patients will be recruited from the Frankel Cardiovascular Center (FCVC) at Michigan Medicine. Opioid-naive patients undergoing first-time, elective cardiac surgery through a full median or miniature sternotomy beginning September 3, 2019, were screened for a targeted enrollment of 154 patients for randomization. Approximately 600 to 750 patients meeting these criteria underwent surgery at Michigan Medicine in 2017. Opioid-naive is defined as opioid-free at the time of preoperative clinic history and physical examination.

Patients lost to follow-up will be censored for data analysis, and missing individual intervention points will be dealt with by multiple imputations, as appropriate. We will compare the clinical and sociodemographic attributes of patients who decline participation and patients lost to follow-up with those of patients with complete follow-up to assess potential responder bias. We estimated a 20% rate of missingness, which was incorporated into our power calculation. On the basis of historical institutional data, we anticipated approaching 5 to 10 patients per week for potential enrollment, with an approximate 5 to 7 month enrollment period within a 12-month study period for completion of clinical follow-up, data analysis, and manuscript production. Although this timeline was affected by the COVID-19 pandemic forcing a pause in enrollment between March 14th and the time of writing, we were 93.5% (144/154) enrolled at the time of pausing and remained optimistic about completing enrollment within our 12-month study period. We used block randomization with randomly variable block sizes generated with Stata 15 software (StataCorp LLC, College Station, TX) and computer randomization occurred with the treatment assignment tool (Treatment Assignment Tool-University of Michigan [TATUM]) from the Michigan Institute for Clinical and Health Research.

Patients were approached, participated in the informed consent process, and were enrolled during the preoperative history and physical appointment, typically after being seen by a member of the advanced practice team. The study coordinator approached potential subjects either in exam rooms or in the clinic waiting room to describe the study and offer participation. Interested patients engaged with the study coordinator and gave informed consent, at which point the coordinator randomized and assigned a sequential subject identification number to each study patient using TATUM (Figure 2).

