In this study, patients randomized to the intervention group will meet the comfort coach in the preoperative clinic (#1), where the coach will perform an introductory emotional, medical, and psychosocial needs assessment to consider the impact of surgery on the patient. The comfort coach will also introduce a *comfort menu* (Multimedia Appendix 1) [56-63] for pain management. After the preoperative clinic visit, the comfort coach will see the patient 5 additional times: at the preoperative bay immediately before surgery (#2), at extubation in the intensive care unit (**#**3), at chest tube removal (#4), at discharge (#5), and at the 30-day clinic follow-up visit (#6). These points of intervention were defined through feedback provided during our initial 11-patient feasibility study. During these intervention points, patients will receive the comfort menu and choose individualized interventions, including guided imagery, guided visualization, focused breathing, distraction techniques, music, art, mindfulness, and patient positioning. Supplies used during comfort coach interventions commonly include music playlists, compassion cards, stress balls, iPad activities, and virtual reality goggles. Additional activities are listed in the comfort menu in Multimedia Appendix 1.

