###### Postsurgical Health Care Utilization

The primary endpoint of this trial is a composite outcome defined as the total number of days spent at home within the first 30 days after surgery. Each partial or full day spent in the hospital (during index or readmission hospitalization), at any extended care facility, emergency room, urgent care center, or doctor’s office for an unplanned visit will be subtracted from 30 to generate the total number of full days spent at home. This number will reflect total health care utilization within the immediate postoperative period, with lower values indicating more utilization. The number of days in an extended care facility, outside hospital emergency room or urgent care visits, and readmissions are routinely discussed at the 30-day postoperative clinic appointment and will be captured through a combination of chart review by 2 study team members and conversations with patients. In addition, the number of telephone calls made by each patient or patient’s family member to the University of Michigan hospital system regarding the clinical concerns of the patient within the first 30 postoperative days will be captured through chart review and independently verified by 2 study team members. If necessary, we will then use Michigan Value Collaborative data to quantify differences in health care utilization by comparing total and component 90-day episode payments among Medicare, Blue Cross Blue Shield of Michigan, and Medicaid beneficiaries, as our team has previously done in both coronary artery bypass (CABG) [31] and aortic valve replacement [30] studies in Michigan.

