##### Power Analysis

Our primary endpoint is composite of health care utilization, defined as the total number of days spent at home within the first 30 days after surgery. Secondary endpoints include mean GAD-7 and PHQ-9, KCCQ-12, Picker Patient Experience Questionnaire, IES-R, and Brief Pain Inventory Scores and mean inpatient and outpatient opioid use.

We will compare mean days with a two-tailed *t* test and set the power of this study at 80% with alpha (Type I error) of .05 and the Cohen *d* effect size (defined as the difference in means divided by standard deviation) between medium (0.5) and large (0.8) [69,70], which yields a minimum sample size of 52 patients to detect a large effect size and 128 to detect a medium effect size [71]. Incorporating 20% missingness, a sample size of 154 patients will adequately detect a medium effect size. We next verified this statistically derived sample size with clinically relevant examples. Although most large series reporting opioid use report the median and interquartile range of OME [47,72], our sample size should be sufficient to satisfy the central limit theorem and use mean values. At our institution, the mean opioid use after sternotomy in 2017 was 200 OMEs. We estimated that to detect a 30% reduction in opioid use (mean 140 OMEs) with a standard deviation of 125 OME in the control and 100 OME in the intervention arms, a sample size of 114 would be required. For composite health care utilization, demonstrating a 3-day difference between the arms with a 6-day standard deviation would detect by a total sample size of 128 patients. With 154 patients, we should have adequate power to detect a difference in our primary outcomes for aims 1 and 2.

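### As written, the missing-data rule drops patients lost before day 30 from the primary t test and directs imputation at coach visits rather than at missing outcomes

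*Protocol article*

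**What the plan says.** Under Patient Enrollment and Randomization, the protocol article gives one sentence on missing data: "Patients lost to follow-up will be censored for data analysis, and missing individual intervention points will be dealt with by multiple imputations, as appropriate". The same paragraph plans to compare the attributes of decliners and of patients lost to follow-up with those of patients followed completely, and gives a 20% allowance for missingness.

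Under Postsurgical Health Care Utilization, the primary endpoint is a "composite outcome defined as the total number of days spent at home within the first 30 days after surgery". Each full or partial day in care "will be subtracted from 30 to generate the total number of full days spent at home". Extended-care days, outside emergency or urgent-care visits and readmissions are topics of the 30-day appointment, and they "will be captured through a combination of chart review by 2 study team members and conversations with patients".

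The Analytic Approach for Aim 2 and the Power Analysis both name a two-tailed t test on mean days. The Power Analysis uses the 20% only to enlarge the sample: "Incorporating 20% missingness, a sample size of 154 patients will adequately detect a medium effect size".

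The Comfort Coach Approach and Interventions uses the term that also appears in the missing-data rule: "During these intervention points, patients will receive the comfort menu and choose individualized interventions".

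**The concern.** Each half of the rule fits the design badly.

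*Censoring.* This concept belongs to time-to-event analysis, and the article has no time-to-event endpoint or method. The primary endpoint is a single number per patient, known only once all 30 days are accounted for. A t test either has that number or leaves the patient out.

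*Imputation.* It is directed at something that, in the article's own vocabulary, is delivery of the intervention. Controls have no coach visits to miss. An intervention patient who misses one has received less treatment, and there is no outcome value to impute. The data that do need a rule are unknown days in care and unreturned surveys, and the sentence does not name them.

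What is at stake is the comparison of the groups as randomised. A patient who is readmitted or in a care facility around day 30 may miss the visit at which outside utilization is discussed. Such patients have few days at home, so leaving them out raises the mean of the arm they belonged to. Intervention patients also have coach contact up to and including the 30-day visit, so retention may differ between arms.

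**Working it through.** **1. The plan's own sample-size figures.** Inputs from the Power Analysis: difference 3 days, SD 6 days, two-sided alpha 0.05, power 80%. A 1:1 allocation is assumed, because the text does not state the ratio.

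- Effect size: d = 3/6 = 0.5.
- The two-sample t test (noncentral t) needs 63.77 per arm, so 64 per arm and 128 in total. This matches the article.
- Inflation: 128 × 1.2 = 153.6, rounded up to 154. This also matches. (Dividing by 0.8 would give 160; that is a separate matter.)

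The 20% therefore enters the plan only as an enlargement of the sample, which fits an analysis of patients with complete data.

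**2. What censoring can mean for this endpoint.** Set "Patients lost to follow-up will be censored for data analysis" beside a count formed by subtraction from 30 and compared by t test.

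- Lost after day 30 but before day 90: the primary endpoint is complete, and nothing in the sentence requires its removal.
- Lost before day 30: the total is incomplete, and the t test has no way to use a partial value. Exclusion is the workable reading.

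**3. What is imputed.** Set "missing individual intervention points will be dealt with by multiple imputations, as appropriate" beside the description of the coach's visits. Taken literally, the object is a visit that exists in one arm only. If survey time-points were meant, the survey scores gain a rule, but the first clause still removes the patients lost to follow-up.

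**4. Size of a possible bias.** Let *p* be the proportion lost in an arm and *L* the number of home days by which lost patients fall short of retained ones. If the retained mean is *c*, the mean of all patients in the arm is (1 − *p*)*c* + *p*(*c* − *L*) = *c* − *pL*. The retained mean is thus too high by *pL*. With the same *L* in both arms, the bias in the difference is *L* × (difference in loss between arms). Neither *L* nor loss by arm is in the document. The values below are assumptions; 3 and 6 days are 0.5 and 1 of the plan's SD.

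| Loss in the two arms | *L* = 3 days | *L* = 6 days |
|---|---|---|
| 20% v 20% | 3 × 0 = 0 | 6 × 0 = 0 |
| 15% v 25% | 3 × 0.10 = 0.3 day | 6 × 0.10 = 0.6 day |
| 10% v 30% | 3 × 0.20 = 0.6 day | 6 × 0.20 = 1.2 days |

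Against the 3-day target the range is 0 to 1.2/3 = 40%. The direction depends on which arm loses more. Higher loss among controls inflates the control mean and understates a benefit; higher loss in the intervention arm does the reverse.

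**5. Numbers and power.** If the full 20% applied to the primary endpoint, 0.2 × 154 = 30.8, or about 31 patients, would be left out and about 123 analysed. Power at d = 0.5 would be about 78.5%, compared with 86.9% if all 154 outcomes were available. An imputed analysis would lie between these. Possible bias matters more here than power.

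**The case against.** The strongest reply is that the sentence is loose rather than wrong. Three of the six coach visits (preoperative clinic, discharge, 30-day visit) coincide with three of the four survey times in Table 1. The Results section uses the word touchpoints for both surveys and coach contacts. Imputing missed surveys, with the qualifier that it be done as appropriate, is a plausible intention. Chart review is not made conditional on attending the clinic, and since March 2020 surveys have been collected by telephone, online or mail, so missing a visit is not the same as being lost. Much of this stands. It makes the second half of the rule a matter of ambiguity and limits the likely size of the problem. It does not rescue the first half: patients lost before day 30 have no defined place in the primary comparison.

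A reader might also infer more than the article supports:

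- *That 31 patients will leave the primary analysis.* The 20% is a general allowance for missingness, not a stated loss on the primary endpoint. About 31 is an upper planning figure.
- *That the comparison of lost with retained patients pools the arms and so would miss differential loss.* The article does not say whether it is done by arm.
- *That chart data on lost patients will be discarded.* This is one consequence of reading the rule as exclusion; the article does not state it.
- *That the result will be biased in favour of the coach.* No direction is established. If the extra coach contact improves retention in the intervention arm, and lost patients have fewer home days, the bias is toward no effect.

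**Conclusion.** The point holds in a limited form. For a patient lost before day 30, the stated rule leaves exclusion as the workable reading for a t test on a day count. The imputation clause, read in the article's own terms, does not reach missing outcomes. Exclusion may be informative and is partly avoidable, since the index stay and in-system readmissions can be taken from the chart.

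The size cannot be fixed from the document. Under the stated assumptions the bias runs from 0 to 1.2 days against a 3-day target. It is zero when loss and the home-day gap are the same in both arms, and it can go in either direction. The planned comparison of lost with retained patients is descriptive and would not change the primary estimate. This is worth correcting before the analysis but ranks below a must-fix.

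**What to change.** Replace the sentence with wording such as:

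> All randomised patients who undergo surgery are analysed in their assigned arm regardless of touchpoints received; patients randomised but not operated on are reported by arm. Touchpoint completion is reported descriptively. Chart-recorded utilization is used for every patient. Missing outcome components and survey scores are multiply imputed by arm from baseline scores and chart data, with a sensitivity analysis for data missing not at random. Complete-case results are secondary.

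Randomisation takes place in the preoperative clinic and the endpoint counts days from surgery. Reporting the patients who are never operated on by arm therefore keeps that exclusion visible.

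Report loss to follow-up by arm, and make the comparison of lost with retained patients within each arm. If the imputation clause was meant for survey time-points, say so in those words.

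The cost is a change of wording and some extra analysis work. No new data collection is needed, because the baseline surveys and chart review are already planned.
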